## Abstract

**Background:**

Stunting and micronutrient deficiencies have persistently affected children in the Brazilian Amazon for decades. However, in recent years, a notable increase in childhood overweight prevalence has been observed, particularly in the context of heightened food insecurity exacerbated by the COVID-19 pandemic. Despite the limited number of effective solutions proposed to tackle this problem, digital interventions have shown great promise worldwide in preventing obesity and promoting healthy diets.

**Objective:**

This study aims to describe the protocol of a family-based WhatsApp intervention, specifically designed to investigate the efficacy of multimedia messaging in preventing excessive weight gain and improving healthy eating practices among school-aged children in the Amazon region.

**Methods:**

This study protocol outlines a theory-driven randomized controlled trial based on the cognitive theory of multimedia learning and the social cognitive theory. A total of 240 parents or caregivers of children enrolled in the Maternal and Child Health and Nutrition Cohort Study in Acre (MINA-Brazil) will be recruited by phone and social media. The intervention group will receive persuasive multimedia messages through WhatsApp over 19 weeks, while the waitlist control group will remain in the usual care. The primary outcome is a change in children’s BMI in *z* score. Secondary outcomes are changes in dietary intake and biochemical indicators of the children. Outcome measures will be assessed at baseline and 5 months after randomization in comparison to usual care. The analysis will use an intent-to-treat approach and will be conducted using the statistical package Stata (version 18.0), with a significance level set at *P*<.05. Paired and unpaired 2-tailed *t* tests will be applied to compare mean changes in the outcomes.

**Results:**

Data collection started in June 2023, and final measurements are scheduled to be completed in December 2023. The results of the main analysis are expected to be available in 2024.

**Conclusions:**

This innovative multimedia message intervention holds significant potential for fostering behavioral changes among Amazonian children.

**Trial Registration:**

Brazilian Clinical Trials Registry RBR-5zdnw6t; https://ensaiosclinicos.gov.br/rg/RBR-5zdnw6t

**International Registered Report Identifier (IRRID):**

DERR1-10.2196/54446

## Introduction

In recent decades, childhood obesity has emerged as a global epidemic [1]. According to the World Health Organization (WHO), more than 340 million children were overweight or obese in 2016 [2]. In addition, with the emergence of the COVID-19 pandemic in 2019, the situation has been aggravated due to school closures, physical inactivity, dietary changes, and mental health disorders [3].

In Brazil, according to the latest national school anthropometric survey, in 2009, 1 out of 3 children were overweight [4]. However, it is expected that due to the COVID-19 crisis and the absence of national child anthropometric surveys for 15 years, the current prevalence of childhood overweight has likely worsened [5,6]. In this context, the Brazilian Amazon was one of the most affected regions in the country due to its remote location and lack of specialized health assistance [5,7]. Recent studies revealed that approximately 70% of the northern population experience food insecurity [8]. Additionally, 20% experience severe food insecurity, wherein individuals feel hungry but do not have funds to buy food, have only 1 meal a day, or endure entire days without any meals [8].

In this scenario, considering the Brazilian economic crisis paired with the neglected fast growth of the ultraprocessed food (UPF) industry, access to fresh food has become challenging, while UPF has become ubiquitous in most food markets [9,10]. UPF are formulations produced exclusively by the food industry through processing techniques that damage the food matrix (eg, extrusion, refining, and prefrying). Additionally, UPFs are frequently high in calories, harmful fats, sugar, and artificial additives [11]. Many studies in the literature have shown that the consumption of UPF may increase the risk of morbidity and early mortality [12]. Therefore, UPF’s high availability and consumption are significantly endorsing a substantial change in Western Brazilian Amazon food patterns, which has placed overweight and obesity as an important public health problem due to the historical rates of stunting and micronutrient deficiencies in the region [13-15]. Although some studies have called attention to the urgent need for early interventions to prevent childhood obesity in the Amazon region, few effective solutions have been proposed to tackle this problem so far [16,17].

Along these lines, digital interventions focused on promoting weight loss and healthy eating behaviors have shown promising results, especially mobile phone interventions (mobile health [mHealth]) [18,19]. MHealth interventions are innovative and have countless advantages. First, it increases the contact between health care professionals and people living in remote areas, such as the Amazon region [20]. Second, it is a low-cost, easy-to-use, and alternative tool that is already widely incorporated into society. Lastly, these interventions can be developed on a large scale, benefiting people in a wide region. Although Amazon is considered a location of poverty and of great inaccessibility, about 80% of the population has access to the internet, and 8 out of 10 adults have a cell phone [21,22].

In this context, multimedia messages have spread rapidly in society in recent years. Since it includes both textual and visual resources, it provides efficient learning due to its greater ability to establish itself in the brain’s long-term memory; therefore, it demonstrates great potential to generate changes in health behaviors, especially in populations with low educational levels [23-26]. As far as we know, no studies have evaluated the effects of multimedia messages on children’s health behaviors; however, there is plenty of evidence indicating the extensive potential of multimedia resources. Randomized controlled trials based on soap operas, video games, and websites as multimedia components have reported a significant increase in fruit and vegetable consumption and a decrease in sugary drinks and sweets consumption [27-33].

Also, a recent systematic review and meta-analysis showed that childhood obesity risk is significantly influenced by parental weight status [34]. Thus, parent-focused interventions are an important key to promoting efficient and lasting changes in children’s eating behaviors. Family-based interventions focusing on children who are overweight that used SMS text messaging lead to a significant reduction in children’s adiposity and BMI [35]. Additionally, healthy eating patterns were improved among all family members [36]. These findings support the hypothesis that family-based multimedia messaging interventions have great potential to promote behavioral changes in children.

This study protocol will be the first to assess the effect of mHealth on dietary practices and anthropometric measurements of Amazonian children. We aim to develop a parenting-focused, mobile-based intervention through multimedia messaging to promote healthy eating habits and prevent obesity among Amazonian children. We also intend to support and provide high-quality evidence to guide future public policy regarding childhood obesity, food insecurity, and sustainable food systems.

## Methods

### Study Aim

The general aim of this study is to evaluate the efficacy of a parent-focused mHealth intervention to change dietary practices and prevent excessive weight gain among school-aged children from the Maternal and Child Health and Nutrition Cohort Study in Acre (MINA-Brazil). Therefore, we hypothesize that children whose parents or caregivers receive nutrition-related multimedia messages will have improvements in BMI in *z* score (BMIz), dietary food intake, and biochemical data.

### Overview and Trial Design

This trial will be a parallel randomized controlled trial nested in MINA-Brazil, the first population-based birth cohort based in Cruzeiro do Sul, Acre State, in the Western Brazilian Amazon. The cohort was designed to investigate the determinants of maternal and child health and have as participants children born at the Hospital Estadual da Mulher e da Criança do Jurua, in Cruzeiro do Sul, in the period between July 2015 and June 2016. Participants have been followed up for 5 years, and the last evaluation of health status took place in 2021. This protocol was prospectively registered in the Brazilian Clinical Trials Registry (RBR-5zdnw6t; date of registration: March 30, 2023; UTN code: U1111-1289-0560) and has been described according to the CONSORT-EHEALTH checklist (version 1.6.1; Multimedia Appendix 1 [37-47]) [48]. Table 1 shows the timeline of the study activities according to the intervention stage:

**Table 1 table1:** Timeline of the study activities according to intervention stages.

Stage of intervention	Recruitment	Baseline	Intervention period	Postintervention
Verbal consent for screening	✓			
Eligibility screening verification	✓			
Study invitation	✓			
Face-to-face individual interview		✓		
Written consent from parents and written assent from children		✓		
Sociodemographic and participant information collection		✓		
Anthropometric measures		✓		✓
Food frequency questionnaire administration		✓		✓
Biochemical data collection		✓		✓
Strengths and Difficulties Questionnaire administration		✓		✓
Short version of the Brazilian Food Insecurity Scale administration		✓		✓
Delivery of an educational booklet		✓		
Goals setting for intervention group			✓	
Multimedia messaging for a 19-week follow-up			✓	
Phone call at 1 week to check if caregivers are properly receiving the messages			✓	
Goal achievement assessment for intervention group				✓
Delivery of same intervention to waitlist control group.				✓

### Study Population and Setting

We will recruit 300 parents or caregivers of children enrolled in the MINA-Brazil birth cohort (Figure 1). They will be contacted by phone calls made from the Laboratory of Telephone Interviews of the Faculty of Public Health of the University of Sao Paulo. Family phone numbers will be assessed from the MINA-Brazil study database. Trained interviewers will make the calls at different times of the day to maximize the chance of contact with parents or caregivers. Additionally, MINA-Brazil’s social media (ie, Facebook and Instagram) will be used to contact families who have changed their phone numbers but have not updated this information in their records. At this first contact, eligibility criteria will be assessed; then, the study’s aim will be explained, and the parent or caregiver will be invited to be part of the study. Following this, a face-to-face meeting will be scheduled at a health care center in Cruzeiro do Sul with children and parents or caregivers to collect the consent forms and conduct the initial interview.

**Figure 1 figure1:**
[figure not shown]
Study flowchart. BMIz: BMI in *z* score; MINA-Brazil: Maternal and Child Health and Nutrition Cohort Study in Acre; MMS: Multimedia Message Service.

Inclusion criteria for the study include (1) being a guardian of a child aged between 7 and 8 years enrolled in MINA-Brazil, (2) owning a cell phone that can install the WhatsApp app, (3) having internet access at least once a week, and (4) being literate and having internet literacy.

Exclusion criteria include (1) dietary restrictions or special diets that limit a child’s ability to eat a variety of foods (eg, children on treatment for any disease that requires a specific diet), (2) simultaneous participation in another nutritional or weight loss program, and (3) not having the availability to follow up on the intervention for the whole period between baseline and final data collection (eg, intending to move out of town).

### Power and Sample Size Calculation

The sample size estimation used the expected effect size (E) of at least 10% change for the mean value of BMIz as the main outcome (*z* score=1.5) and SD of 3.5 in a 2-tailed distribution, considering a *P* value of .05, statistical power of 80% (β=20%), and sample size ratio (group 1/group 2) of 1:1. Thus, for the expected E/SD ratio, the minimum sample required must be 100 participants per group [49]. However, assuming a dropout rate and potential losses of 20% during the intervention period, the sample size to be enrolled at baseline will be at least 120 children per study group [49].

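### The stated inputs (10% of a mean BMIz of 1.5, SD 3.5) do not give 100 children per group, and the trial cannot be described as powered for a 10% change

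*Protocol article*

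**What the plan says.** The section Power and Sample Size Calculation defines the effect as an "expected effect size (E) of at least 10% change for the mean value of BMIz as the main outcome" and gives the numerical inputs as "score=1.5) and SD of 3.5 in a 2-tailed distribution". The error rates are a "value of .05, statistical power of 80% (β=20"%), with a "sample size ratio (group 1/group 2) of 1:1". It concludes that "for the expected E/SD ratio, the minimum sample required must be 100 participants per group", raised to at least 120 per group to allow for 20% losses. The E/SD ratio itself is not printed, and no source is given in the text for the 1.5 or the 3.5; a reference is cited for the sample size step.

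The abstract says "The primary outcome is a change in children’s BMI in" z score. The Data Analysis section compares mean changes with t tests and mentions no covariate adjustment. The Results section reports 266 children enrolled at baseline.

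**The concern.** The paragraph supplies every input of a two-sample calculation, so the result can be checked, and it does not follow from the inputs. This is the only power statement for the primary outcome. If it stands, readers will believe that the trial had 80% power for a 10% change in BMIz. They may then give a non-significant result more weight against such a change than it deserves, and they cannot tell what difference the trial could detect.

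The SD raises a second doubt. A z score has an SD of about 1 in its reference population, so 3.5 is hard to accept for BMIz. The text also does not say whether 3.5 describes BMIz at one visit or its change, and the change is what will be analysed.

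**Working it through.** **Inputs.** From the sample size section: mean BMIz 1.5, change of 10%, SD 3.5, two-sided .05, power 80%, 1:1. From the Results section: 266 enrolled.

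**Formula.** n per group = 2 × (1.960 + 0.842)² / d² = 15.70 / d², with d = E/SD. The two-sample t test adds about one child per group.

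**1. Attempt to reproduce 100.**

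| Reading | E | d = E/SD | n, normal formula | n, t test |
|---|---|---|---|---|
| 10% of the mean | 0.10 × 1.5 = 0.15 | 0.15/3.5 = 0.0429 | 8,547 | 8,548 |
| 1.5 is the effect itself | 1.5 | 1.5/3.5 = 0.4286 | 86 | 87 |
| Ratio that gives 100 | 0.40 × 3.5 = 1.40 | 0.40 | 99 | 100 |

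Neither reading of the stated inputs gives 100. For E = 0.15, a one-sided test needs 6,733 per group and a paired or one-sample test about 4,276, so those variants do not help. If 1.5 is the effect, it is a 10% change only of a mean of 1.5/0.10 = 15, which no mean BMIz can plausibly be.

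**2. Power at the stated inputs.** With 100 per group, E = 0.15 and SD 3.5, the two-sided t test has power 6.0%, barely above the 5% significance level. (Counting only rejections in the direction of the effect, a normal approximation gives 4.9%.) For E = 1.5 the power is 85%.

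**3. What 100 per group detects.** At 80% power the t test detects d = 0.398. At SD 3.5 this is 0.398 × 3.5 = 1.39 z units, and 1.39/1.5 = 93% of the assumed mean. The required number for a 10% change is 8,548/100, about 85 times the stated one.

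**4. The SD.** If BMIz were normal (an assumption) with mean 1.5 and SD 3.5, the points one SD from the mean would be 1.5 + 3.5 = 5 and 1.5 − 3.5 = −2. About 16% of children would then lie above z = 5 and about 16% below z = −2.

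**5. With the children enrolled.** Assuming an equal split, 266/2 = 133 per group, and 133 × 0.8 is about 106 after 20% loss. The detectable standardised difference is 0.39. Power for 0.15 at SD 3.5 is still 6%.

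**6. If the SD of change is smaller.** The article gives no such SD, so the values below are assumptions. All are for 100 per group.

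| Assumed SD of BMIz change | Detectable difference (0.398 × SD) | Power for 0.15 |
|---|---|---|
| 0.4 | 0.16 | 75% |
| 0.5 | 0.20 | 56% |
| 0.6 | 0.24 | 42% |
| 1.0 | 0.40 | 18% |

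An SD of about 0.38 is the largest for which 100 per group has 80% power for 0.15.

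**The case against.** The strongest defence is that the SD of 3.5, and not the number of children, may be the faulty input. Change in BMIz over five months may vary far less than 3.5, and then 100 per group could be a sensible size. This stands as far as it goes: the 6% is the power at the printed inputs and is no estimate of the trial's real power. A reader might infer that the trial needs 8,548 children per group or has almost no power. The document does not support that, because both figures depend on the SD that is in doubt. Nor does it rescue the claim, since an SD of change near 0.38 or below would be needed and none is stated.

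A reader might also infer that the mean of 1.5 was used as the effect. That is not established: 1.5/3.5 gives 87, and reaches 100 only if 0.43 is also rounded down to 0.40. Another guess is that the inputs are raw BMI values, since 10% of 15 is 1.5. The article does not say so, and if it were true the calculation would concern a different variable from the primary outcome. Which error was made cannot be determined from the document.

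It is also tempting to say that the SD of change must be smaller than the SD of BMIz. With equal variances at the two visits, this requires a baseline-to-follow-up correlation above 0.5. That is likely over five months, but no figure is given.

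Finally, enrolment has taken place and the planned t tests do not use 1.5 or 3.5. So the analysis is unaffected, and a confidence interval would show what a null result excludes. This limits the damage to the power claim, but that claim is still wrong in print.

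**Conclusion.** The sample size justification is wrong as written. Its own inputs require about 8,548 children per group, and 100 per group gives about 6% power for the stated effect. The figure of 100 corresponds to E/SD of about 0.40, or 1.39 z at SD 3.5, a ratio that the stated inputs do not give. This rests only on the printed inputs and a standard two-sample t test.

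The SD of 3.5 has no stated source, is implausible for a z score, and is not tied to change in BMIz. What the trial can detect in z units remains unknown until an SD of change is given. Over the assumed range of 0.4 to 0.6 it is 0.16 to 0.24 with 100 per group. The paragraph must be corrected. The error lies in the stated justification, and the finding does not show that too few children were enrolled.

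**What to change.** Withdraw the justification built on 10%, 1.5 and SD 3.5, and do not describe the trial as powered for a 10% change. Replacement text could read:

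*With 100 children per group completing follow-up, a two-sided 5% test has 80% power for a standardised difference of 0.40 in the change in BMIz. With the 266 children enrolled and 20% loss (about 106 per group), this difference is about 0.39.*

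Then express this in z units with a sourced SD of BMIz change. The birth cohort is a possible source if it holds suitable repeated measurements. The article reports five years of follow-up with a last evaluation in 2021, which does not show BMIz measured about five months apart at age 7 to 8. Failing that, state the SD as an assumption with a range, as in step 6 of the working, and say whether differences of that size would matter for these children, because 0.40 is derived from the sample size and not from relevance.

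The cost is one rewritten paragraph and one SD, estimated or assumed. No extra children are needed and the analysis does not change. The drawback is a less favourable power statement.

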## Results

Data collection started in June 2023, and 266 children were enrolled at baseline. Final measurements are scheduled to be completed in December 2023. The results of the main analysis will be conducted in 2024 and are expected to be available in 2024 and 2025.

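### The enrolment floor of 120 per group leaves 96 after the plan's own 20% loss, short of its stated minimum of 100; the planned totals of 240 and 300 are also not reconciled

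*Protocol article*

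**What the plan says.** The Power and Sample Size Calculation section of the protocol article gives a minimum of 100 participants per group for 80% power at a two-sided 5% level with 1:1 allocation. It then makes an allowance, "assuming a dropout rate and potential losses of 20% during the intervention period", and concludes that "the sample size to be enrolled at baseline will be at least 120 children per study group".

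Totals appear in three other places:

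- Abstract, Methods: "A total of 240 parents or caregivers of children enrolled" in the cohort are to be recruited by phone and social media. This is 2 x 120.
- Study Population and Setting: "We will recruit 300 parents or caregivers of children enrolled in the MINA-Brazil birth cohort", by the same two routes and with a reference to the flowchart in Figure 1.
- Results: "266 children were enrolled at baseline".

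**The concern.** An allowance for loss exists so that the required number remains once the loss has occurred. Here the minimum, the loss rate and the enrolment floor are given together, and the floor does not protect the minimum. A trial that enrolled exactly 120 per group and lost exactly 20% would have followed the plan and still missed its own requirement.

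The planned total also depends on the section read. The final report will be compared with a planned size, and a reader will find 240 in one place and 300 in another, both described as recruitment.

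**Working it through.** **Inputs** (Power and Sample Size Calculation): minimum n = 100 per group; loss d = 0.20; enrolment floor 120 per group; two-sided alpha 0.05; power 80%; SD 3.5; effect described as a 10% change in mean BMIz with a z score of 1.5. From Results: 266 enrolled.

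**1. Reproducing the printed floor.**
- n x (1 + d) = 100 x 1.20 = 120. This matches.
- n / (1 - d) = 100 / 0.80 = 125. This does not match.

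The article prints no formula, so multiplication by 1.2 is an inference, though it gives the printed figure exactly.

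**2. What the floor delivers.**
- Remaining after 20% loss: 120 x 0.80 = 96 per group (192 in total), 4 per group short.
- Largest loss that keeps 100: 1 - 100/120 = 16.7%.
- Floor consistent with 20% loss: 125 per group, 250 in total.

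**3. Effect on power, conditional on the base of 100.** The article does not state the effect-to-SD ratio that leads to 100, so it has to be inferred.
- Normal approximation: E/SD = (1.960 + 0.842) x sqrt(2/100) = 0.396 gives exactly 80% at 100 per group. At 96 per group, power = Phi(0.396 x sqrt(96/2) - 1.960) = 78.4%.
- t test at E/SD = 0.40: 80.4% at 100 and 78.7% at 96.

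Either way the loss is about 1.6 points.

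**4. The same check at the printed inputs.** These can be read in two ways, and neither gives 100 (two-sided t test).

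| Reading of effect | E/SD | n per group for 80% | Power at 96 |
|---|---|---|---|
| 1.5 | 1.5/3.5 = 0.43 | 87 | 84.0% |
| 10% of 1.5 = 0.15 | 0.15/3.5 = 0.043 | 8,548 | about 6% |

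**5. Enrolment achieved.** 266 is above 250. Assuming an equal split (133 per group), 133 x 0.80 = 106.4, so about 106 per group remain after 20% loss. The loss that would still leave 200 in total is 1 - 200/266 = 24.8%.

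**6. Totals side by side.** 240 (abstract) and 300 (Study Population and Setting) are both future-tense recruitment figures for the same population. 266 is a count of children already enrolled.

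**The case against.** The best defence has four parts.

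- **The 120 is a floor, and events have overtaken it.** Enrolment reached 266, more than the corrected 250, so nothing in the design, conduct or analysis has to change. This stands and is why the point is minor. It does not repair the printed calculation, since a floor is the number meant to secure the requirement.
- **The power loss depends on a ratio that the article never gives.** This also stands. A reader might infer that the enrolment target fails to deliver 80% power. The document does not support that as a general statement. With an effect of 1.5 and the printed SD, 96 per group gives 84.0%. With an effect of 0.15, power is about 6% and an error of four per group hardly matters. The 1.6-point loss holds only at the inferred ratio of about 0.40.
- **The 300 may be the pool of families contacted.** The Methods place it at the phone-contact stage, before eligibility and consent, and tie it to a flowchart that is not shown here. Table 1 separates recruitment from baseline. This reading is plausible, but the abstract uses the same verb for 240, so the text leaves the two unreconciled.
- **The corrected 125 rests on a base of 100 that the printed inputs do not reproduce.** This is right, and 125 should be offered only on that condition. The internal mismatch between 100, 20% and 120 remains whatever the correct base is.

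**Conclusion.** The point holds and is minor. A minimum of 100, a loss of 20% and a floor of 120 cannot all stand: the floor is 5 per group (10 in total) below what the plan's own loss rate requires. The arithmetic is certain, given that the 20% applies to those enrolled. The power consequence, about 78.4% to 78.7% instead of about 80%, assumes that 100 per group was meant to give about 80%.

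The recruitment totals conflict in one respect only, 240 against 300. A reader might count 266 as a third inconsistent total. It is not one: it is enrolment achieved, and it contradicts neither the printed floor nor the corrected target. That 266 leaves about 106 per group at 20% loss assumes an equal split, because the Results give only the total.

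**What to change.** Issue a short correction to the article:

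1. Give the enrolment floor as 125 per group (250 in total) for 20% loss, or state that 120 per group allows for 16.7% loss. Keep the printed 120 visible as the prespecified figure, because a target restated after 266 were enrolled should not read as the advance plan.
2. Make the 125 conditional on the base of 100, and check that base against the stated effect and SD. If it changes, recompute the floor as n/(1 - 0.20).
3. Label 240 and 300 by stage (enrolled and approached), if that is what they are, and use the labels consistently in the abstract and Methods.
4. Note that the 266 enrolled, if split equally, leave about 106 per group at 20% loss.

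The cost is a text correction. No extra enrolment is needed.
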